### Intervention

This study will consist of one baseline session and two study phases, Phase A and Phase B. The timing of the assessments and study phases that will be conducted is illustrated in Fig. 1.

**Fig. 1 Fig1:**
[figure not shown]
A schematic outline of the assessments that each participant will undertake during the TRACED study

#### Phase A

Phase A will consist of two separate study days, where participants will be randomised to either receive the ATD (i.e. an amino acid beverage lacking TRP) or BAL (which will consist of an ATD-based amino beverage plus TRP). Each study day will be separated by a maximum of 7 days. For each study day of Phase A, participants will be required to undertake a drug and pregnancy screen (if female), will be administered the respective amino acid challenge beverages (ATD and BAL), and a series of psychological and cognitive assessments (see below). A total of seven blood samples will also be taken per study day in phase A. The type of assessments and rationale for the blood samples are further described below in more detail.

##### Amino acid challenge composition

The Moja-De ATD protocol (i.e. the ATD protocol that has been demonstrated to be safe for use in the child and adolescent population) employs amino acid administration within an aqueous suspension as a beverage, in which the relevant amino acid quantities are linked to the participant’s body weight. The amino acid quantities in ATD Moja-De are (dosage per 10 kg of body weight) as follows: L-phenylalanine (1.32 g), L-leucine (1.32 g), L-isoleucine (0.84 g), L-methionine (0.5 g), L-valine (0.96 g), L-threonine (0.6 g) and L-lysine (0.96 g). The respective control condition is known as the BAL condition. The BAL beverage contains the same amino acid quantities as described above for the ATD condition, but with an additional 0.7 g of TRP per 10 kg of body weight [23]. Research has shown that ATD is a safe and effective serotonergic challenge procedure [8, 15], and that it can be safely used in minors (Moja-De ATD test protocol) [12–14, 24].

Both the ATD and the BAL amino acid mixtures will be prepared by an approved manufacturing facility. The ATD amino acid beverage is made up of the seven dry amino acids as per the above calculations. Each subject receives a proportional amount of ATD amino acids within an aqueous suspension according to their body weight. For example, a 80 kg subject will receive 200 ml SyrSpend® SF (purified water modified food starch, sodium citrate, cinic acid, mali c acid, sodium benzoate, sulcralose, simethicone and cherry flavour) with the respective amino acids related to the individual’s body weight. As outlined above, the BAL beverage is made up of the same seven amino acids in the ATD with the addition of TRP (a total of eight amino acids) in the same way as the ATD beverage. Each subject receives a proportional amount of BAL amino acids within an aqueous suspension according to their body weight. Following the administration of both ATD/BAL beverages, apple juice will be offered following the mixture to wash out the taste.

##### Biochemical assessments and psychological and cognitive tasks to be conducted in Phase A

Several assessments and cognitive tasks will be conducted in Phase A, as outlined in Fig. 1. Assessments include the sampling of blood, mood assessments and cognitive testing.

The primary purpose of the blood samples collected at the beginning of Phase A is to assess baseline levels of TRP and other amino acids. The blood samples that will be collected during the two study days will allow measurement of the relevant amino acids contributing to the depletion. At the beginning of each study day in Phase A, participants will be required to complete the Beck Depression Inventory II (BDI-II) [25], the Hamilton Depression Rating Scale (HDRS) [26] and the Children’s Depression Rating Scale – Revised (CDRS-R) [27]. On the first study day, parents or caregivers will also complete the Child Behaviour Checklist [28]. Mood will be monitored on the two study days through the use of the Profile of Mood States (POMS) after ATD or BAL administration, in 30-min time intervals [29].

Cognitive assessments that will be conducted in Phase A include the Tests for Attentional Performance (TAP, PSYTEST, Herzogenrath, Germany) [30]. The TAP subtests that will be used include Alertness, Working Memory, Divided Attention and Sustained Attention. Between each test there will be a break of approximately 10 min. The Facial Expression Recognition Task will also be conducted on each study day of Phase A [31], as well as a Reversal Learning Task [32].

#### Phase B

Phase B will commence between 24 and up to a maximum of 72 h after the second day of Phase A. Phase B will consist of a 12-week open label pharmacological treatment as usual with the SSRI fluoxetine. Participants will be required to attend weekly follow-up sessions with the study doctors. Fluoxetine will be prescribed and administered in a fixed-dose approach, in accordance to the NICE Clinical Guidelines – Treatment of Depression in Children and Young People [33]. Specifically, the administration of fluoxetine will start at 10 mg daily and will be increased to 20 mg daily after 1 week.

During this second phase (Phase B), participants are free to participate in other treatments such as psychological treatment or psychotherapy (e.g. cognitive behavioural therapy) if medically indicated, and will not be excluded from the study unless the treatment with fluoxetine is stopped. However, these additional treatments will be taken into consideration with the statistical analysis and may lead to post-hoc exclusion of some participants. Under this approach, the data obtained will largely reflect the clinical reality in the sample served.

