### Subjects and eligibility criteria

This pilot study aims to recruit *N* = 20 participants, and all participants who are referred to the study will be screened. Inclusion criteria for this study are as follows: adolescents aged between 12 and 17 years with a confirmed diagnosis of MDD (ICD-10 or DSM-5; diagnosis to be confirmed through the administration of the Kiddie Schedule for Affective Disorders and Schizophrenia (K-SADS) [21], as well as a full psychiatric assessment), no current suicidal ideation or suicidal plans, no other psychiatric co-medications at study entry, IQ > 85 (screened through the use of the Wechsler Abbreviated Scale of Intelligence (WASI-II) [22]), and no active or past eating disorder. Exclusion criteria include current abuse of alcohol and use of illicit substances, pregnancy in female participants, chronic medical or neurological disorders, subjects whose primary language is not English, treatment with other histaminergic or dopaminergic medications, disorders of amino acid metabolism, and contraindications against the use of fluoxetine. Participation in this study is entirely voluntary. Once recruited, participants will be able to withdraw their consent at any time by informing the study team.

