#### Recruitment

Participants will be recruited mainly via Headspace Services, which is a National Youth Mental Health Foundation that provides early intervention mental health services to 12–25 year olds, and Princess Margaret Hospital. Additionally, local paediatricians, developmental and health services, and general practitioners will participate in identifying suitable participants. Participants who discontinue from the study will be replaced and will be sourced by the same recruitment processes.

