#### Power analysis

As this study is being conducted within a cohort of adolescents, we expect there to be possibly smaller effects [34], which could be due to reduced neurochemical effects, as well as difficulties with subjective mood ratings by the participants. For *N* = 20 participants, a power of 0.97 was calculated (ANOVA, effect for within-subjects factors) to detect small effects (effect sizes of 0.4) with a significance level of α = 0.05 (two-tailed testing, critical F = 3.26). This is in line with previous research showing that mood effects observed after ATD can be rather small in healthy subjects, but possibly more severe in patients affected or vulnerable to depression [35, 36]. Power calculations were performed with G*Power Software, Version 3.1.3 [37]. It is important to note, however, that these calculations are preliminary (conducted before study initiation) and are currently an estimate. The data of this study can be used to inform future larger scale studies. Individuals who are drop-outs or lost to follow-up will be replaced to meet the power calculations.

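### Exclusion on stopping fluoxetine, criterion-free post-hoc exclusion for added treatment, and replacement of leavers let the Phase B results be selected on the outcome

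*Protocol article*

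**What the plan says.** All the rules are in the protocol article.

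- **Phase B, stopping fluoxetine.** Participants may take up other treatments such as psychotherapy and "will not be excluded from the study unless the treatment with fluoxetine is stopped". Stopping fluoxetine therefore ends study participation.
- **Phase B, added treatment.** Where other treatment is medically indicated, "these additional treatments will be taken into consideration with the statistical analysis and may lead to post-hoc exclusion of some participants". No criterion, timing or blinding of the decision is given.
- **Recruitment.** "Participants who discontinue from the study will be replaced and will be sourced by the same recruitment processes". There is no limit by phase or by reason.
- **Power analysis.** "Individuals who are drop-outs or lost to follow-up will be replaced to meet the power calculations".
- **Subjects and eligibility criteria.** "This pilot study aims to recruit *N* = 20 participants".

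The article does not say whether the data of excluded or replaced participants stay in any analysis. The second objective (Study objectives and hypotheses) is to test whether the ATD mood effect from Phase A predicts improvement 12 weeks into open-label fluoxetine.

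**The concern.** The outcome to be predicted is improvement on fluoxetine. Stopping the drug, dropping out and being given further treatment can each follow from not improving. The Background expects non-response in up to 40%, so the group in which these events may cluster is not small. If those participants leave the analysis and others take their place, the count of 20 is restored but the sample is not. It then consists of people who stayed on fluoxetine and did not need much else.

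The post-hoc exclusion is a second and separate problem. Phase B is open label, no criterion is fixed, and nothing ties the decision to a time before outcomes are seen. With 20 participants, leaving a few in or out can change the result, and a reader of the final report could not tell whether the choice was influenced by the data.

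**Working it through.** **1. The plan's own figure.** The Power analysis states "a power of 0.97 was calculated (ANOVA, effect for within-subjects factors" and "to detect small effects (effect sizes of 0.4) with a significance level of α = 0.05 (two-tailed testing, critical F = 3.26". Using λ = N·m·f²/(1 − ρ) with assumed m = 3 measurements, ρ = 0.5, two groups and sphericity, λ = 20 × 3 × 0.16 / 0.5 = 19.2. With 2 and 36 degrees of freedom the critical F is 3.26 and power is 0.972. The stated figure reproduces, so the point is about who is analysed and not about this arithmetic.

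Under the same assumptions, with no replacement, power is 0.92 with 16 analysed, 0.88 with 14 and 0.81 with 12. The ANOVA calculation does not depend on replacing leavers.

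**2. Response among completers.** The article gives no drop-out or co-treatment rates, so these are illustrations. Take a true response rate p = 0.60 (the complement of 40%), and let 10% of responders and a share q of non-responders stop. Response among completers = 0.60 × 0.90 / [0.60 × 0.90 + 0.40 × (1 − q)].

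- q = 0.10: 0.54 / 0.90 = 60% (no bias)
- q = 0.30: 0.54 / 0.82 = 66%
- q = 0.50: 0.54 / 0.74 = 73%

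**3. The prediction result.** Assume the ATD mood effect and improvement are bivariate normal with true r = 0.5.

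*Worst case, lowest 20% on improvement all removed.* The cut is at z = −0.842. Mean shift = φ(z)/0.8 = 0.280/0.8 = 0.35 SD. Remaining variance of improvement = 1 − 0.842 × 0.350 − 0.350² = 0.583. Then r = √[0.25 × 0.583 / (0.25 × 0.583 + 0.75)] = √(0.146/0.896) = 0.40. By Fisher's z, power at N = 20 is Φ(atanh(r)·√17 − 1.96): 0.62 for r = 0.5 and 0.42 for r = 0.40.

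*Softer selection, 20% removed.* Removal follows a logistic model in improvement with slope 1 to 2 per SD. By simulation r is 0.48 to 0.45, and mean improvement rises by 0.17 to 0.26 SD.

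*About 30% removed, logistic.* If removal depends on improvement only, r = 0.47. If it also depends on the ATD mood effect, r = 0.40 or 0.54 according to the sign of that dependence. With a true r of 0, the same two cases give about −0.10 and +0.10.

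**4. Discretionary exclusion.** Simulate no association, N = 20 and 6 co-treated participants chosen independently of outcome (20,000 trials, t-test of the correlation). The single analysis of all 20 rejects in 4.8%. Reporting the better of all participants and co-treated excluded rejects in 7.6%. Choosing among four cut-offs (0, 2, 4 or 6 excluded) rejects in about 9%. The simulation standard error near 7.6% is √(0.076 × 0.924 / 20,000) = 0.2 percentage points.

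**The case against.** The strongest reply is that replacement is a recruitment rule, and that leaving the study is not the same as deletion from the dataset. Analysis sets may be defined in a full protocol or analysis plan that is not shown. That is fair as far as it goes: a reader might infer that the trial will certainly analyse completers only, and the article does not say so. But it does fix exclusion on stopping, an undefined post-hoc exclusion, and replacement tied to the power calculation. These are stated rules, and followed as written they permit the selection described.

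Three further inferences are tempting and are not supported.

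- **Phase A data must be lost as well.** Week 12 is listed as a level of the time factor in Data preparation and statistical analysis. However, that section plans a series of ANOVAs and does not mention complete-case deletion. The ATD and control drinks are given only in Phase A, so their contrast needs no week-12 value.
- **All non-responders, up to 40%, will be removed.** No rule excludes for non-response, and co-treatment leads only to possible exclusion.
- **Fluoxetine benefit will be overstated and the correlation weakened.** Equal loss in responders and non-responders gives no bias in response, and the correlation can rise as well as fall.

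It may also be said that this is a pilot, that Phase B has one arm, and that no randomised comparison is broken there. All three are true. Yet the prediction hypothesis is tested in Phase B, and the article offers the data to inform larger studies, which would take over any distorted estimate. The tension with the aim of reflecting clinical practice is slight, because both that aim and the exclusion are worded with room to spare.

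**Conclusion.** The concern holds in this form: the stated rules allow outcome-related and data-dependent selection in Phase B. The size and direction of any bias cannot be derived from the article. Mean improvement is overstated on the condition that poor responders leave or are excluded more often: by 0.17 to 0.26 SD under the softer selection of 20%, and 0.35 SD in the worst case. An assumed correlation of 0.5 lands between about 0.40 and 0.54 across the scenarios tried.

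The post-hoc exclusion is a defect whichever way selection runs, because it needs no link between co-treatment and outcome: about 7.6% error in place of 5%, given 6 co-treated of 20 and a free choice between two analyses. The correlation test used for this is itself an assumption, since the article names none.

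**What to change.** - Delete the post-hoc exclusion. Record added treatments, and state in advance whether they enter as an adjustment or a sensitivity analysis.
- Analyse Phase B in all who start fluoxetine, with a mixed model on the weekly BDI, HDRS, CDRS-R and POMS ratings already planned. Continue these ratings after fluoxetine is stopped, where the participant agrees.
- State that Phase A is analysed in all randomised participants with post-drink data, whatever happens in Phase B.
- If replacement is kept for recruitment, keep the data of replaced participants and report their number and reasons.

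The cost is a few sentences, somewhat more analysis work and a few extra ratings. The changes concern data collection and analysis only and alter no treatment rule.

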##### Biochemical assessments and psychological and cognitive tasks to be conducted in Phase B

Blood, mood and cognitive measurements will also be taken in Phase B. During Phase B, blood samples will be taken. The purpose of the blood testing during Phase B is to monitor fluoxetine availability throughout the course of the study. Fluoxetine levels assessed during this phase will also allow the calculation of preliminary dose–response relationships regarding the suggested predictors of treatment response. Compliance with the fluoxetine treatment will also be monitored through an empty packet return and verbal report. Blood samples will undergo basic laboratory processing before storage in an electronically lockable freezer at –80 °C degrees, before analysis. Participants’ mood will be measured on a weekly basis, using the BDI, HDRS, CDRS-R and POMS. Additionally, the Child Behaviour Checklist will be administered during the 6- and 12-week follow-up of Phase B to assess psychopathology. The cognitive tasks that were completed during each study day of Phase A will also be completed at the 12-week follow-up of Phase B. These tasks include the TAP, the Facial Expression Recognition Task and the Reversal Learning Task.

## Expected outcomes

### Mood

We expect that ATD-induced mood changes (Phase A) when compared to baseline and BAL administration will be inversely related to the mood-based treatment response to fluoxetine (as assessed via the POMS) and improvements in depressive symptomatology (BDI, HDRS, CDRS-R) 12 weeks into treatment (Phase B). In particular, our assumption is that symptom severity at baseline and change in mood following the ATD challenge will be proportional to mood change due to fluoxetine treatment as response to ATD may be an index of serotonergic vulnerability for mood changes.

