ATD is a neurodietary method used to lower brain 5-HT synthesis, and works on the premise that the essential amino acid tryptophan (TRP) is the physiological precursor of brain 5-HT synthesis. As brain 5-HT can only be synthesised through the availability of TRP in the central nervous system, the consumption of foods or beverages lacking in TRP leads to a respective decline in central nervous 5-HT synthesis. ATD involves the administration of an amino acid mixture lacking in TRP after an overnight protein fast. The administered amino acids compete with endogenous TRP on the uptake into the central nervous system over the blood–brain barrier, which leads to decreased substrate availability for central nervous 5-HT synthesis for a period of several (usually 5–7) hours. Additionally, the administered amino acids stimulate protein synthesis in the liver, which takes TRP from plasma stores and also contributes to depletion (for a detailed review, see Dingerkus et al. [8]).

ATD has been shown to decrease mood in depressed adults in remission, particularly those using antidepressants, but not in healthy controls [9]. Mood response to ATD reliably predicted depressive episodes during a follow-up year [10]. Additionally, ATD reversed antidepressant-induced remission in a large proportion of a study sample involving adults with depressive symptoms [11]. Given its history of temporarily reversing remission amongst treated depressed adults, it may be that ATD is particularly potent amongst those who are responsive to SSRIs.

The impact of ATD on mood has only been investigated in adults, mostly because safe and effective ATD methods targeting central nervous 5-HT synthesis in young people were only recently demonstrated [12–14]. In order to make ATD suitable for use in young people, it must account for body weight. A body weight-adapted ATD procedure, called Moja-De, has been validated in rodents [15] and humans [8], but has never been used to investigate mood-related antidepressant treatment response in adolescents with MDD.

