#### Data preparation and statistical analysis

The data that will be collected will consist of information relating to medical history, mood, scores on cognitive tasks and blood samples. All data, including blood samples will be de-identified. Codes for the depletion (ATD) and sham depletion (BAL) will be held in an envelope in a securely locked space in the unlikely event of an emergency that requires the code to be broken. Only researchers on the listed research team will have access to the final dataset.

To examine changes in response to ATD (mood, cognitive parameters and tasks, amino acid concentrations, etc.) as well as after treatment (mood symptoms, cognition, SSRI monitoring) a series of repeated measures ANOVAs will be conducted with time (baseline, ATD administration and 12 weeks into treatment) and challenge procedure (ATD/BAL administration) as within-subject factors. We will also evaluate for a significant effect of relevant baseline amino acid levels on the observed changes. If such a significant interaction is discovered, ANCOVAs will be performed with baseline values as covariates.

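### If one baseline score enters both the ATD mood change and the fluoxetine response, zero is the wrong null correlation (about 0.5 in size for POMS against POMS), and the plan does not fix the direction it expects

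*Protocol article*

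**What the plan says.** The protocol article, Expected outcomes, Mood, expects that "ATD-induced mood changes (Phase A) when compared to baseline and BAL administration will be inversely related to the mood-based treatment response to fluoxetine" on POMS, and to "improvements in depressive symptomatology (BDI, HDRS, CDRS-R) 12 weeks into treatment (Phase B". The next sentence puts the relation differently: "symptom severity at baseline and change in mood following the ATD challenge will be proportional to mood change due to fluoxetine treatment". Neither sentence gives a sign convention for the two changes or names the score from which response on fluoxetine is measured.

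Data preparation and statistical analysis plans repeated measures ANOVAs with "time (baseline, ATD administration and 12 weeks into treatment" as the levels of time, and ATD/BAL as the second within-subject factor. There is one baseline level. The article writes no model that relates one change to the other.

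The rationale is in the Background: "it may be that ATD is particularly potent amongst those who are responsive to SSRIs".

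On measurement, Phase A mood is followed with the "Profile of Mood States (POMS) after ATD or BAL administration, in 30-min time intervals". For the depression scales, "At the beginning of each study day in Phase A, participants will be required to complete the Beck Depression Inventory II (BDI-II", together with HDRS and CDRS-R. In Phase B, "Participants’ mood will be measured on a weekly basis, using the BDI, HDRS, CDRS-R and POMS".

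**The concern.** The second objective is to see whether the mood effect of ATD predicts response to fluoxetine. The ATD effect is taken at least partly against baseline, the response is naturally also a change from baseline, both are on POMS, and the analysis section offers one baseline level to serve both. A participant whose baseline score happens to be high by measurement error then appears to have lower symptom scores both after ATD and at week 12. The two changes move together for a reason unrelated to serotonin, and an association judged against zero is judged against the wrong value.

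The claim about baseline severity has a similar weakness, because a change from baseline contains the baseline.

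The wording adds to the problem. One sentence says *inversely related* and the next says *proportional*. With no coding given, it is not settled which sign of an observed association would count as support.

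**Working it through.** **The plan's own figure.** The article gives no figure for this association. Its only related number is the power of 0.97 for the within-subjects ANOVA. That reproduces with N = 20, f = 0.4, α = 0.05 and, as assumptions, 3 measurements, correlation 0.5 and 2 groups: λ = 0.4² × 20 × 3 / (1 − 0.5) = 19.2, df 2 and 36, critical F 3.259 (stated 3.26), power 0.972. It concerns a mean difference over time, not prediction.

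**Inputs.** N = 20 is from the article. It gives no variances or between-occasion correlations, so these are assumed: equal variances σ² and a common correlation ρ, with departures tried below. Let B = baseline, A = after ATD, L = after BAL, F = week 12. The ATD change can only be on POMS, because the other three scales are taken at the start of the study day.

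**Step 1: shared baseline, no predictive effect.**
- cov(A − B, F − B) = var(B) − cov(B,F) − cov(A,B) + cov(A,F) = σ²(1 − ρ).
- Each change has variance 2σ²(1 − ρ).
- Correlation = σ²(1 − ρ) / [2σ²(1 − ρ)] = **+0.50**, whatever ρ is.
- Reversing one change (A − B against B − F) gives **−0.50**.

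In 40,000 simulated null trials of N = 20 for each of ρ = 0, 0.5 and 0.8 (critical |r| = 0.444), a test of zero correlation rejected in 64% of trials, essentially all in the direction of the artefact.

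**Step 2: which way this pushes.** The rationale is that a larger mood drop on ATD goes with a larger improvement on fluoxetine.

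| Coding | Sign the rationale predicts | Artefact |
|---|---|---|
| Both post minus baseline | negative | +0.50 |
| Worsening on ATD against improvement | positive | −0.50 |

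In either coding the artefact opposes the hypothesis.

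**Step 3: other definitions, same assumptions.**
- ATD minus BAL directly, A − L against F − B: 0.00, with rejection at about 5%.
- Each day corrected by its own baseline (B on the ATD day, B_L on the BAL day), (A − B) − (L − B_L) against F − B: covariance σ²(1 − ρ), variances 4σ²(1 − ρ) and 2σ²(1 − ρ), so 1/√8 = 0.35, with rejection in about 34%.
- Separate Phase B baseline, A − B against F − P: 0.00.

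**Step 4: relaxed assumptions.**
- A and F related only through B: √[(1 − r_AB)(1 − r_BF)] / 2. For r_AB from 0.5 to 0.9 and r_BF from 0.2 to 0.6 this runs from 0.32 down to 0.10.
- A different outcome scale, with within-scale correlation 0.5 and cross-scale correlation k on the same occasion and c on different occasions: (k − c) / [2(1 − 0.5)]. With c = 0.4 and k = 0.5, 0.6 or 0.7 this is 0.1, 0.2 or 0.3.

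**Step 5: baseline severity against change, same scale.** corr(B, B − F) = σ²(1 − ρ) / [σ × σ√(2(1 − ρ))] = √[(1 − ρ)/2]. For ρ = 0.3, 0.5 and 0.7 this is 0.59, 0.50 and 0.39. Here the sign does agree with the stated expectation.

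**The case against.** A reader might infer more: that measurement noise alone would let the trial report that ATD predicts response, in about 64% of trials. The documents do not support this. Step 2 shows that the artefact runs against the rationale in the Background and in the second sentence of the Mood section. It would imitate prediction only if *inversely related* meant that more worsening on ATD goes with less improvement, which contradicts both places.

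Four further objections have weight:

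- **The shared baseline is not stated.** The article has a baseline session, scales at the start of both study days, and weekly Phase B scores. A separate Phase B baseline would remove the coupling. This stands as a condition, although the single baseline level makes sharing the natural reading.
- **BAL is already named as a comparator.** True, but the text says baseline *and* BAL. A double difference that keeps the baseline is still coupled at 0.35; only the direct contrast is free of it.
- **No change-on-change test is written, and a prediction model may sit in the full protocol or SAP.** That stands, so 64% is not an error rate of a planned test. The hypothesis is nevertheless stated as an association between two changes, and the point concerns how the article defines them.
- ***Inversely* and *proportional* can be reconciled**, as signed changes in opposite directions with related magnitudes. That is probably the intent, but the text does not say so.

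Nor is the baseline-severity link guaranteed to appear: severity may be on another scale, and 0.39 lies below the critical value of 0.444 at N = 20.

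**Conclusion.** The point holds conditionally. If one baseline score enters both changes, zero is the wrong null value. The null correlation is 0.5 in size for POMS against POMS under equal variances and a common correlation. It is about 0.1 to 0.3 under the other correlations and scales tried, and zero if Phase B has its own baseline. Given the article's rationale, the likely harm is a masked true relation, not a false confirmation.

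An association of baseline severity with change on fluoxetine is expected at about 0.4 to 0.6 on a common scale, for assumed correlations of 0.7 to 0.3, so it is not evidence of prediction. The two descriptions of direction should become one signed statement.

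**What to change.** 1. Define the predictor as POMS on the ATD day minus POMS on the BAL day at matched times after the drink, with no baseline term. Its null correlation is zero provided that ATD-day and BAL-day scores relate equally to baseline and to week 12 when ATD predicts nothing.
2. Model the week-12 score with its pre-fluoxetine value as covariate, instead of change from the shared baseline, and name the assessment that supplies that value.
3. Do not count a link between baseline severity and change as evidence of prediction.
4. Replace the two descriptions of direction with one signed hypothesis: greater worsening on ATD than on BAL goes with a lower baseline-adjusted week-12 symptom score.

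The cost is wording only. The post-drink POMS scores and week-12 scores are already scheduled, and the baseline score is one that the planned ANOVAs already rely on.
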